## Abstract

**Background:**

Patients with advanced colorectal cancer (CRC) commonly receive irinotecan-based systemic treatment to alleviate symptoms, improve quality of life (QoL), and prolong overall survival (OS). However, predicting efficacy and toxicity of the treatment is challenging. Previous research indicated an association between the tumor molecular profile and response to irinotecan-based systemic treatment. Moreover, the *UGT1A1* genotype of the patient, and the activity of the gut microbial enzyme β-glucuronidase (GUS) have been suggested as biomarkers for the development of systemic (e.g. neutropenia) and gastrointestinal toxicity (e.g. diarrhea) respectively. Therefore, the OPTIMA study will evaluate in patients with advanced CRC: 1) whether tumor molecular profiling can predict the efficacy of irinotecan-based systemic treatment; 2) whether high bacterial GUS enzyme activity is associated with increased gastrointestinal toxicity, decreased QoL and OS; as well as 3) the safety of a 70% irinotecan dose intensity in UGT1A1 poor metabolizers (PMs).

**Methods:**

This prospective, observational, multi-center cohort study will include patients with advanced CRC scheduled for irinotecan-based systemic treatment. Archived tumor tissue and routine CT/MRI scans at baseline and after four cycles will be used to investigate the association of tumor molecular profile and treatment response according to RECIST. Before treatment initiation, germline DNA obtained from whole blood will be genotyped using PCR to determine the *UGT1A1*28* genotype, followed by 30% irinotecan dose reduction in UGT1A1 PMs. Bacterial GUS activity will be quantified in fecal samples collected before and during treatment by means of an enzyme activity assay and will be related to patient-reported gastrointestinal toxicity (mainly diarrhea). Additionally, patients will fill in questionnaires concerning QoL, medication use, medical history and comorbidities, dietary habits, as well as physical performance. OS will be documented, capturing the duration from the start of treatment until death from any cause.

**Discussion:**

Results obtained in the context of the OPTIMA study are expected to contribute to the optimization of efficacy and the reduction of toxicity of irinotecan-based systemic treatment, thereby potentially improving QoL of patients. Given that maintaining QoL is particularly critical in the palliative setting, the OPTIMA study has the potential to be of significant benefit for patients and their caregivers.

**Trial registration:**

This trial is registered in the ClinicalTrials.gov register (NCT05655780) on December 16th, 2022.

## Background

Colorectal cancer (CRC) represents a major public health concern as it is the third most frequently diagnosed cancer and the second cause of cancer-related mortality worldwide [1]. In 2022, 21% of patients with newly diagnosed CRC in the Netherlands suffered from metastatic disease [2]. In this group of patients, irinotecan-based systemic treatments are commonly applied to relieve symptoms, improve quality of life (QoL) and extend overall survival (OS).

However, the individual response to irinotecan-based treatment differs consistently between patients, and is currently largely unpredictable. Previous research indicated that molecular tumor characteristics might be associated with response to irinotecan-based systemic treatment. CRC can be subdivided into four consensus molecular subtypes (CMS1-4), based on different gene expression profiles [3]. Ten Hoorn et al. concluded based on a meta-analysis that specifically in CMS4 metastatic disease, patients benefit more from irinotecan-based regimens compared with oxaliplatin-containing regimens [4].

An additional disadvantage of irinotecan-based systemic treatment is the occurrence of systemic (primarily neutropenia) and late-onset gastrointestinal (GI) toxicity, (primarily diarrhea). For instance, grade 3–4 neutropenia has been previously identified in 46% and grade 3–4 diarrhea in approximately 18% of patients [5, 6]. The occurrence of severe toxicity often leads to irinotecan dose reduction, or premature discontinuation of the treatment. This negatively affects not only the patient’s QoL and OS, but also puts significant pressure on family and caregivers, as well as on hospitalization-related healthcare costs [7]. Consequently, there is an urgent need for biomarkers to identify patients at risk for developing irinotecan-induced toxicity. In this context, two promising candidate biomarkers are 1) the UDP Glucuronosyltransferase Family 1 Member A1 (*UGT1A1*) genotype of the patient and 2) the microbial enzyme β-glucuronidase (GUS).

UGT1A1 is the main liver enzyme responsible for inactivation of SN-38 (the active metabolite of irinotecan) by conjugating it with glucuronic acid, resulting in SN-38G [8]. Certain *UGT1A1* polymorphisms (*UGT1A1*28* and *UGT1A1*93*) have been shown to be associated with reduced enzyme activity and an increased risk to develop neutropenia [8–10]. To prevent this toxicity, the clinical utility of *UGT1A1* genotyping with subsequent initial genotype-guided dose adaptation has been demonstrated [8]; however, is not yet routinely recommended in Dutch clinical guidelines [11].

The microbial enzyme GUS is expressed by certain gut bacteria [12]. GUS enzymes can remove glucuronic acid for microbial use as a carbon source, and in this way re-activate the inactive SN-38G into the cytotoxic SN-38 in the intestinal lumen [13]. This reactivation process has significant clinical implications, potentially resulting in severe mucosal damage and diarrhea [14]. Preclinical studies have demonstrated that the inhibition of GUS might be a promising method to limit SN-38-induced GI toxicity [15, 16]. However, this association has not been investigated in humans yet and requires further investigation. In addition, there are hundreds of different GUS enzyme variants found in human stool samples, with a broad diversity in structures, and functionality [12, 17, 18]. Therefore, it also remains to be established which specific microbes exert SN-38G-specific GUS activity and are related to irinotecan-induced GI toxicity in CRC patients.

In view of the studies described above, the tumor molecular profile, *UGT1A1* genotype and bacterial GUS are promising molecular markers for the prediction of irinotecan efficacy and toxicity. Therefore, the OPTIMA study aims to evaluate 1) whether tumor molecular profiling (e.g. CMS classification, transcriptomics) can predict the efficacy of irinotecan-based systemic treatment and is associated with QoL and OS, and 2) whether UGT1A1-guided dose reduction in UGT1A1 poor metabolizers (PMs) is safe to use, and 3) whether high GUS enzyme activity is associated with GI toxicity, decreased QoL and OS in patients with metastatic or unresectable CRC. These insights will greatly contribute to more personalized irinotecan-based treatment regimens as well as well-considered choices for other treatment options.

## Methods and study design

### Aims of the study

The primary objectives of this study are:To investigate whether tumor molecular markers can predict the response to irinotecan-based systemic treatment and are associated with QoL and OS;To validate the safety of *UGT1A1* genotype-guided dose adaptation (70% dose intensity) in UGT1A1 PMs;To assess whether high bacterial GUS enzyme activity is associated with irinotecan-induced GI toxicity, decreased QoL and OS

The most important secondary objectives of this study are:To investigate the dynamics in GUS activity and overall gut microbiota composition, diversity and functional capacity during irinotecan-based systemic treatment;To assess associations between GUS activity and gut microbiota composition, diversity and functional capacity,To measure fecal levels of SN-38 and SN-38-G and to determine its association with gut microbiota composition, bacterial GUS activity, *UGT1A1* genotype, treatment response and toxicity;To correlate tumor molecular profile, GUS activity and other clinical characteristics (e.g. physical performance and nutritional status) during irinotecan-based systemic treatment.

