#### Study population

Patients will be included via the oncologic outpatient clinics of the participating centers. Patients are eligible if they are ≥ 18 years of age, diagnosed with advanced CRC, and planned to start with irinotecan-based systemic treatment, if applicable in combination with anti-EGFR treatment. Additionally, patients must have a WHO performance status 0–2, minimal acceptable safety laboratory values at baseline, defined as: ANC of ≥ 1.5 × 109/L, platelet count of ≥ 100 × 109/L, serum bilirubin ≤ 1.5 × ULN, ALAT and ASAT ≤ 2.5 × ULN; in case of liver metastases ALAT and ASAT ≤ 5 × ULN, and renal function (eGFR) ≥ 50 ml/min or creatinine ≤ 1.5 × ULN.

Exclusion criteria are: microsatellite instability (MSI) or deficient MMR proteins, being pregnant or nursing, presence of an ileostomy, Asian ethnicity, other systemic treatment within < 1 month before inclusion, therapeutic antibiotic use within < 3 months before inclusion, abdominal radiotherapy within < 2 weeks before inclusion, being physically or mentally incapable or incompetent, more than 25% irinotecan dose reduction at the start of treatment (dose reductions during treatment are allowed), with exception of dose reduction in UGT1A1 PMs.

Patients can be treated with combination chemotherapy (FOLFOXIRI/FOLFIRI) or irinotecan monotherapy and will follow the regular treatment regimens, according to the Dutch guidelines (Table 1).

**Table 1 Tab1:** Overview of irinotecan-based treatment regimens

		**Compounds**	**Number of weeks per cycle**	**Possible addition of bevacizumab?**	**Possible addition of anti-EGFR?**
Treatment	FOLFOXIRI	Irinotecan 5-FU Folinic acid Oxaliplatin	2	yes	no
	FOLFIRI	Irinotecan 5-FU Folinic acid	2	yes	yes
	Monotherapy	Irinotecan	3	no	no

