#### UGT1A1 genotyping in blood samples and adaptation of irinotecan dose intensity

Before treatment initiation, the *UGT1A1* genotype of the patient will be assessed in blood using Polymerase Chain Reaction (PCR). Patients will be genotyped for *UGT1A1*28* (TA repeat; rs3064744; NC_000002.12:g.233760235TA[5_11]). DNA for genotyping will be isolated from 200µl of whole EDTA blood obtained prior to start of therapy. Genotyping will be conducted using validated real-time PCR reactions with appropriate wild type, heterozygous and homozygous controls in every run. Genotypes will be converted to phenotypes in the following manner: homozygous carriers of *UGT1A1*28* are defined as UGT1A1 PMs, heterozygous carriers are considered UGT1A1 intermediate metabolizers (IMs) and *UGT1A1* wild type individuals are considered UGT1A1 normal metabolizers (NMs). In UGT1A1 PMs the irinotecan starting dose will be reduced by 30% and further individualized in subsequent cycles of treatment based on ANC and clinical tolerance. The starting dose in UGT1A1 NMs and IMs will be left unchanged. Further dose modifications or treatment delays will be applied according to standard of care protocols and guidelines.

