In addition, the main outcome parameters will be correlated to fecal levels of SN-38 and SN-38G, as well as other clinical variables of interest, as assessed by the questionnaires.

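### Comparing absolute fecal SN-38 and SN-38G levels between UGT1A1 poor metabolizers and other patients mixes genotype with the 30% starting-dose reduction; the genotype association needs a dose-normalised variable

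*Protocol article*

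**What the plan says.** Under Aims of the study, the secondary objectives of the protocol article include "To measure fecal levels of SN-38 and SN-38-G and to determine its association with gut microbiota composition, bacterial GUS activity". The sentence continues with UGT1A1 "genotype, treatment response and toxicity", so genotype is one of the named correlates. The analysis section for the main outcome parameters returns to this in one sentence: "the main outcome parameters will be correlated to fecal levels of SN-38 and SN-38G", together with other clinical variables. Neither place mentions a dose-normalised level, a metabolite ratio or an adjustment for dose.

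The section on UGT1A1 genotyping and dose intensity sets the dose by genotype: "In UGT1A1 PMs the irinotecan starting dose will be reduced by 30% and further individualized in subsequent cycles of treatment". For the other two groups, "The starting dose in UGT1A1 NMs and IMs will be left unchanged". The Study population section excludes patients with "more than 25% irinotecan dose reduction at the start of treatment (dose reductions during treatment are allowed), with exception of dose reduction in UGT1A1 PMs". The section on fecal samples states that both analytes are measured by LC–MS/MS.

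**The concern.** The amount of drug and metabolite in feces can be expected to depend on how much irinotecan was given. Here the genotype determines the starting dose. A PM versus non-PM comparison of absolute levels therefore estimates the genotype effect and the dose effect together.

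The direction matters. The Background section describes UGT1A1 as the enzyme that conjugates SN-38 to SN-38G, with reduced activity in *28 carriers. If that carries through to feces, PMs should have more SN-38 and less SN-38G for a given dose. A lower dose pushes both analytes down, so it hides the first effect and enlarges the second. A null SN-38 result could follow from the dose rule alone, and a low SN-38G in PMs could appear with no genotype effect at all.

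**Working it through.** **Inputs from the protocol article**
- PM starting dose: reduced by 30%, so 1 − 0.30 = 0.70. This reproduces the 70% dose intensity stated in the Abstract and the Aims.
- NM and IM starting dose: unchanged, 1.00. The lowest value eligibility allows is 1 − 0.25 = 0.75.
- Later cycles: doses are individualised in PMs and may be modified in anyone.
- Evaluable patients: 84 (Sample size calculation).

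**Assumptions not in the documents**
- Fecal levels are proportional to dose.
- For the last step only: a *28 allele frequency q of 0.25 to 0.40 with Hardy–Weinberg proportions.

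**1. Can dose as a covariate separate the effects?** Take cycle 1 within one regimen, everyone on the protocol dose, and columns for intercept, IM, PM and relative dose. The rows are (1, 0, 0, 1.0) for NM, (1, 1, 0, 1.0) for IM and (1, 0, 1, 0.7) for PM. The rank is 3 with 4 columns, because relative dose = 1 − 0.3 × PM. The PM effect and the dose effect are not separately estimable there. One NM starting at 0.80, or one PM record at a different later dose, restores rank 4. At the start, however, the dose ranges do not overlap (0.70 against 0.75 or more). Later changes in PMs follow neutrophil counts and tolerance, so they are tied to toxicity.

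**2. Size of the distortion.** Observed PM/non-PM ratio = true per-dose ratio × (PM dose ÷ non-PM dose).
- Non-PMs at full dose: factor 0.70, or ln(0.70) = −0.357 on the log scale.
- Non-PMs all at the eligibility floor: 0.70 ÷ 0.75 = 0.93. This is the extreme case, since the unchanged dose is the rule.

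With the factor 0.70:

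| True per-dose PM/non-PM ratio | Observed in absolute levels |
|---|---|
| 1.00 (no genotype effect) | 0.70 |
| 1.20 | 0.84 |
| 1.43 (= 1 ÷ 0.70) | 1.00 |
| 1.60 | 1.12 |
| 0.70 (a lower SN-38G) | 0.49 |

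The true ratios are illustrations; the documents give none.

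**3. IM versus NM.** Both groups start on an unchanged dose, so the factor is 1.00 ÷ 1.00 = 1.00.

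**4. How much rests on the PMs?** With 84 patients the expected counts are 84q² PMs, 84 × 2q(1 − q) IMs and 84(1 − q)² NMs.
- q = 0.25: 5.25 PMs, 31.5 IMs, 47.25 NMs. The sum of squares of allele count is 31.5 with PMs. Without them it is 47.25 × 31.5 ÷ 78.75 = 18.9, so 60% is kept.
- q = 0.40: 13.4 PMs, 40.3 IMs, 30.2 NMs. The sum of squares is 40.3 with PMs. Without them it is 30.2 × 40.3 ÷ 70.6 = 17.3, so 43% is kept.
- If PMs stay in a per-allele trend on absolute log levels, the slope is shifted by q × ln(0.70). That is −0.089 to −0.143, a factor of 0.91 to 0.87 per allele.

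**The case against.** The strongest reply is that the article does not commit to comparing unadjusted absolute levels by genotype. It states an objective and one sentence of analysis, both analytes are measured, and a statistical analysis plan that is not shown may already normalise. That is fair, and silence on covariates alone would not be a finding. What remains is that the article names the variable, levels, and also fixes a genotype-driven dose. Taken together as written, they give a confounded PM contrast.

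Several stronger readings are tempting, and the documents do not support them:
- **That the genotype association cannot be answered at all.** IMs and NMs start on the same dose and can be compared on absolute levels.
- **That genotype and dose are inseparable throughout.** Strict aliasing holds only at the start, within a regimen. Non-PMs may start with up to a 25% reduction and doses move later, although those changes are a weak basis for separating the effects.
- **That the associations with toxicity and response are artefacts too.** A lower dose that lowers luminal drug is real exposure, and dividing by dose would remove signal.
- **That the GUS correlation is biased.** The assay adds SN-38G to fecal lysate in the laboratory, and nothing in the article links the dose rule to GUS activity.
- **That absolute levels should never be compared between PMs and non-PMs.** Whether PMs on the reduced dose reach exposure similar to the others is a useful companion to the safety objective.
- **That the SN-38:SN-38G ratio alone solves the problem.** The Background says luminal GUS turns SN-38G back into SN-38, so GUS moves the fecal ratio whatever the genotype.

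**Conclusion.** The concern holds for one contrast. PM versus non-PM in absolute fecal SN-38 or SN-38G is confounded with the starting-dose reduction, and an observed difference, or its absence, should not be read as a genotype effect. Under dose proportionality with non-PMs at full dose, the PM/non-PM ratio is multiplied by 0.70; the factor would be 0.93 only if all non-PMs started at the eligibility floor. This masks a higher SN-38 and exaggerates a lower SN-38G in PMs. IM versus NM is untouched by the rule. The size rests on proportionality, which the documents do not state. The confounding itself needs only that fecal levels depend on dose. The point concerns a secondary objective and its analysis, and does not question the dosing rule.

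**What to change.** For the association with UGT1A1 genotype:
- Make the level divided by the irinotecan dose actually given in that cycle the main variable, for SN-38 and for SN-38G. State the proportionality assumption.
- Use the SN-38:SN-38G ratio as a supporting variable, in which dose cancels under the same assumption. Adjust it for the measured GUS activity.
- Report IM versus NM separately from the comparisons that involve PMs.

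Keep absolute levels for the toxicity and response associations and as a description of exposure in PMs on the reduced dose. Add a sentence that an absolute PM versus non-PM difference will not be interpreted as a genotype effect.

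The cost is small: analysis wording, with no new samples or assays. The dose given has to be extracted for each cycle with a fecal sample, and a rule is needed for values below the limit of quantification, particularly where SN-38G is the denominator of the ratio.

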### Study design

OPTIMA is a prospective, observational, multi-center cohort study conducted at the Maastricht University Medical Centre + (MUMC +, Maastricht), Catharina Hospital (Eindhoven), VieCuri Medical Center (Venlo), Amsterdam University Medical Center (AUMC, Amsterdam), Van Weel-Bethesda Hospital (Dirksland), Hospital Gelderse Vallei (Ede) and Rode Kruis Hospital (Beverwijk), all situated in the Netherlands. The study will be conducted according to the guidelines of the Declaration of Helsinki and Good Clinical Practice and is approved by the Medical Ethics Committee of azM/UM (METC 2022–3247)and the Institutional Review Board of MUMC + (RvB/301756/ReWi). This study has been registered in the ClinicalTrials.gov register (NCT05655780). All patients will sign written informed consent prior to enrollment.

#### Study population

Patients will be included via the oncologic outpatient clinics of the participating centers. Patients are eligible if they are ≥ 18 years of age, diagnosed with advanced CRC, and planned to start with irinotecan-based systemic treatment, if applicable in combination with anti-EGFR treatment. Additionally, patients must have a WHO performance status 0–2, minimal acceptable safety laboratory values at baseline, defined as: ANC of ≥ 1.5 × 109/L, platelet count of ≥ 100 × 109/L, serum bilirubin ≤ 1.5 × ULN, ALAT and ASAT ≤ 2.5 × ULN; in case of liver metastases ALAT and ASAT ≤ 5 × ULN, and renal function (eGFR) ≥ 50 ml/min or creatinine ≤ 1.5 × ULN.

Exclusion criteria are: microsatellite instability (MSI) or deficient MMR proteins, being pregnant or nursing, presence of an ileostomy, Asian ethnicity, other systemic treatment within < 1 month before inclusion, therapeutic antibiotic use within < 3 months before inclusion, abdominal radiotherapy within < 2 weeks before inclusion, being physically or mentally incapable or incompetent, more than 25% irinotecan dose reduction at the start of treatment (dose reductions during treatment are allowed), with exception of dose reduction in UGT1A1 PMs.

Patients can be treated with combination chemotherapy (FOLFOXIRI/FOLFIRI) or irinotecan monotherapy and will follow the regular treatment regimens, according to the Dutch guidelines (Table 1).

**Table 1 Tab1:** Overview of irinotecan-based treatment regimens

		**Compounds**	**Number of weeks per cycle**	**Possible addition of bevacizumab?**	**Possible addition of anti-EGFR?**
Treatment	FOLFOXIRI	Irinotecan 5-FU Folinic acid Oxaliplatin	2	yes	no
	FOLFIRI	Irinotecan 5-FU Folinic acid	2	yes	yes
	Monotherapy	Irinotecan	3	no	no

#### Sampling time points

The sampling period encompasses the first six cycles of irinotecan-based systemic treatment. Before treatment initiation, patients will collect the first (baseline) fecal sample and fill out baseline questionnaires. Additionally, routine computed tomography (CT) or magnetic resonance imaging (MRI) scan as well as *UGT1A1* genotyping will be conducted. Afterwards, patients will enter the regular treatment cycles of irinotecan-based systemic treatment. During the first six cycles, they will regularly collect fecal samples and complete follow-up questionnaires (Table 2). The exact number of weeks between sampling time points might vary, depending on the treatment regimens and potential treatment delays. If available, archived tumor tissue will be used for molecular tumor profiling.

**Table 2 Tab2:** Sampling timepoints of the OPTIMA study

		**Inclusion**	**Baseline**	**Cycle 1**	**Cycle 2**	**Cycle 3**	**Cycle 4**	**Cycle 5**	**Cycle 6**
Regular treatment	Hospital visit	X	X	X	X	X	X	X	X
	Archived tumor tissue		X						
	CT/MRI		X				X		
	Blood sample for UGT1A1		X						
Study related	Questionnaires		T1				T5		T6
	Fecal sample		T1	T2	T3	T4	T5		T6

### Sample collection and analysis

#### Tumor molecular profiling

If archived tumor samples are available from prior surgery or biopsy, the molecular profile of the tumor will be quantified using RNA sequencing for CMS classification and a DNA panel for mutational characterization. Therefore, a workflow will be generated using DNA/RNA from formalin-fixed paraffin-embedded (FFPE) tissues. These samples will be analyzed using RNA sequencing and the TruSight Oncology 500 (TSO500) assay, utilizing the Illumina NovaSeq6000 platform. The CMS classification of the tumor will be characterized based on a recently established FFPE CMS classification algorithm [19]. The TSO500 targets somatic variants over 523 relevant cancer genes.

